### **8.3 Data Monitoring Committee**

A Data Monitoring Committee (DMC) will be established prior to the randomization of the first patient; the same DMC will be used in any other Novartis-sponsored trials evaluating RAD001 in TSC-related diseases. The DMC is an external independent group including at least two physicians with expertise in TSC and one statistician. The DMC will perform the first safety review approximately 6 months after randomization of the first patient in any of the Novartis-sponsored RAD001 trials in TSC, and every 6 months thereafter, unless otherwise requested by the Chairman of the DMC. The DMC will also receive reports on a regular basis on all SAEs reported for this trial. No interim analysis is planned. Recruitment will not be interrupted unless otherwise requested by the Chairman of the DMC.

The responsibilities of the DMC include:

- Minimizing the exposure of patients to an unsafe therapy or dose
- making recommendations for changes in study processes where appropriate
- advising on the need for dose adjustments because of safety issues
- endorsing continuation of the study.

It will be the responsibility of the DMC to review the results of safety data 6 months after randomization of the first patient and every 6 months thereafter and to make recommendations to continue, modify or stop the study based on these results. The DMC will also receive detailed safety reports at regular intervals.

Details on the membership, responsibilities and working procedures of the DMC are described in the Data Monitoring Committee charter.

### **8.4 Steering Committee**

The general role of the steering committee is to provide guidance on study conduct, to help ensure delivery of study data and to develop study-related publications in accordance with the Novartis publication and authorship policy. The steering committee will support the Novartis clinical team on a continuous basis when questions arise in the trial. The steering committee will monitor and supervise the progress of the trial towards its objectives. The committee will be appointed by Novartis and will include two principal investigators from this trial, Novartis staff and possibly other clinical experts. The committee will be chaired by one of the two principal investigators.

The steering committee chair will play a specific role in controlling the flow of trial information, in being the primary contact to receive recommendations from the DMC at any safety review and in further communicating this information appropriately, as described in the DMC charter.

## **9 Data review and data management**

### **9.1 Site monitoring**

Before study initiation, at a site initiation visit or at an investigator's meeting, a Novartis representative will review the protocol and CRFs with the investigators and their staff. During the study, the field monitor will visit the site regularly to check the completeness of patient records, the accuracy of entries on the CRFs, the adherence to the protocol and to Good Clinical Practice, the progress of enrollment, and to ensure that study drug is being stored, dispensed, and accounted for according to specifications. Key study personnel must be available to assist the field monitor during these visits.

The investigator must maintain source documents for each patient in the study, consisting of case and visit notes (hospital or clinic medical records) containing demographic and medical information, laboratory data, electrocardiograms, and the results of any other tests or assessments. All information on CRFs must be traceable to these source documents in the patient's file. The investigator must also keep the original informed consent form signed by patient (a copy is given to the patient).

The investigator must give the monitor access to all relevant source documents to confirm their consistency with the CRF entries. Novartis monitoring standards require full verification of the presence of informed consent, adherence to the inclusion/exclusion criteria, documentation of SAEs, and the recording of data that will be used for all primary efficacy and safety analyses. Additional checks of the consistency of the source data with the CRFs are performed according to the study-specific monitoring plan. No information in source documents about the identity of the patients will be disclosed.

### **9.2 Data collection**

Designated investigator staff must enter the information required by the protocol onto the Novartis CRFs that are printed on 3-part, non-carbon-required paper. The PK summary pages of the CRF will also include an additional non-carbon required page, which will be sent to the bioanalytics pharmacokinetics group by the field monitor. All other summary pages will also include an additional non-carbon page that will be sent to Novartis by the field monitor. Field monitors will review the CRFs for completeness and accuracy and instruct site personnel to make any required corrections or additions. The CRFs are forwarded to the Contract Research Organization (CRO) by field monitors or by the investigational site, with one copy being retained at the investigational site. Once the CRFs are received by the CRO, their receipt is recorded, the original copy is placed in Central Files, and the non-carbon-required copy is forwarded to the responsible data management staff for processing.

The investigator must certify that the data are complete and accurate by signing a memo that will be sent to him/her by the CRO after the last transfer of the data prior to analysis. After database lock, the investigator will receive a memo detailing the obvious corrections that were made to the data.

Blood samples for laboratory data and biomarkers will be collected by sites and sent to a central laboratory for processing. The laboratory results will be sent electronically to the designated CRO.

Results from at home pregnancy test will be recorded in patient diaries for source documentation only.

Radiological imaging will be transmitted by the sites to the CRO designated by Novartis to undergo central radiological review.

Following implementation of amendment 3, menstrual status will be collected monthly via patient diary for source documentation. Every 12 weeks, data from patient diary will be collected at clinical site for CRF. It is recommended that study coordinators contact patients monthly for the first 3 months to remind patients to document menstrual status in patient diary.

### **9.3 Database management and quality control**

The designated CRO staff will review the CRFs entered by investigational staff for completeness and accuracy and instruct the site personnel to make any required corrections or additions. Obvious errors will be corrected by the designated CRO personnel. Queries will be sent (faxed) to the investigational site using a paper Data Query Form. Designated investigator site staff should respond to the query and make any necessary changes to the data. Site personnel will complete and sign the faxed copy and fax it back to the CRO staff who will make the correction to the database. The signed copy of the Data Query Form is kept at the investigator site.

Concomitant medications entered into the database will be coded using the WHO Drug Reference List, which employs the Anatomical Therapeutic Chemical (ATC) classification system. Medical history/current medical conditions and adverse events will be coded using the Medical Dictionary for Regulatory Activities (MedDRA) terminology.

Laboratory samples will be processed centrally and the results will be sent electronically to the designated CRO.

Randomization codes and data about all study drug dispensed to the patient will be tracked using IWRS. The system will be supplied by a vendor, who will also manage the database. The data will be sent electronically to the designated CRO.

PK blood samples collected by sites will be shipped to Novartis for processing. The PK blood collection times will be entered by sites onto the CRFs. The PK blood sample results will be merged with the CRF PK blood collection times and analyzed by Novartis in accordance with internal Novartis procedures.

Blood samples for biomarkers will be collected and sent to a central laboratory for processing. The results will be sent electronically to the designated CRO.

At the conclusion of the study, the occurrence of any emergency code breaks will be determined after return of all code break reports and unused drug supplies to Novartis. The occurrence of any protocol deviations will be determined. After these actions have been completed and the database has been declared to be complete and accurate, it will be locked and the treatment codes will be unblinded and made available for data analysis. Any changes to the database after that time can only be made by joint written agreement between the Global Head of Biostatistics and Statistical Reporting and the Global Therapeutic Area Head.

## **10 Statistical methods and data analysis**

The data will be analyzed by Novartis. Any data analysis carried out independently by the investigator should be submitted to Novartis before publication or presentation.

It is planned that the data from all centers that participate in this study will be used so that an adequate number of patients will be available for analysis.

### **10.1 Populations for analysis**

The **Full Analysis Set (FAS)** consists of all randomized patients. Following the intent-to-treat principle, patients are analyzed according to the treatment and stratum that they were assigned to at randomization. The FAS will be the primary population in the assessment of efficacy.

The **Per Protocol Set (PPS)** will consist of all patients from the FAS without any major protocol deviation, who are evaluable for efficacy and who have completed a minimum exposure requirement. However, if a patient progressed, discontinued for adverse event or died before the minimum exposure requirement could be met, or before he/she was evaluated for efficacy, that patient will still be included in the PPS. Patients will be evaluable for efficacy if they have a known angiomyolipoma response status. The minimum exposure requirement is defined as having a relative dose intensity over the first 12 weeks of treatment of at least 50%. The PPS will be used for a supportive analysis of the primary endpoint.

The **Safety Population** will consist of all patients who received at least one dose of study treatment and had at least one post-baseline safety assessment (where the statement that a patient had no adverse event (on the Adverse Events CRF) constitutes a safety assessment). Patients will be analyzed according to treatment received.

### **10.2 Patient demographics/other baseline characteristics**

Demographic and other baseline characteristics will be listed and summarized by treatment group using the FAS.

Qualitative data (e.g., gender, race, WHO performance status) will be summarized by means of contingency tables for each treatment group, and quantitative data (e.g., age, body weight) will be summarized by appropriate descriptive statistics (mean, standard deviation, median, minimum and maximum) for each treatment group.

### **10.3 Treatments (study drug, concomitant therapies, compliance)**

#### **10.3.1 Study medication**

Duration of study treatment exposure, cumulative dose, dose intensity and relative dose intensity will be summarized by treatment group. The number of patients with dose changes/interruptions will be presented by treatment group, along with reasons for the dose change.

#### **10.3.2 Concomitant therapies**

Concomitant medications and significant non-drug therapies taken concurrently with the study drugs will be listed and summarized by ATC class, preferred term and treatment arm by

means of frequency counts and percentages. These summaries will include medications starting on or after the start of study treatment or medications starting prior to the start of study treatment and continuing after the start of study treatment.

Any prior concomitant medications or significant non-drug therapies starting and ending prior to the start of study treatment will be listed.

The safety population will be used for all above mentioned concomitant medication tables and listings.

## 10.4 Primary objective

The primary objective is to compare the angiomyolipoma response rate on RAD001 versus placebo in patients with angiomyolipomata associated with either TSC or sporadic LAM.

### 10.4.1 Variable

The primary endpoint of this study, angiomyolipoma response rate, is defined as the proportion of patients with an angiomyolipoma response, as defined in [Section 7.5.2](#), using data from the Independent Central Radiological Review of CT/MRIs and the Adverse Events CRF page (to identify angiomyolipoma-related bleeding of grade 2 or worse as defined by NCI CTCAE version 3.0).

### 10.4.2 Statistical hypothesis, model, and method of analysis

The primary analysis will be a comparison of the angiomyolipoma response rates in the RAD001 and placebo arms using an exact Cochran-Mantel-Haenszel (CMH) test at the one-sided 2.5% level, analyzed in the Full Analysis Set. The test will be stratified by the protocol stratification factor, which has three categories as follows: (1) TSC as underlying disease and patient using enzyme-inducing anti-epileptic drugs (EIAED) at randomization, (2) TSC as underlying disease and patient not using EIAED at randomization, and (3) sporadic LAM as underlying disease.

The statistical hypotheses are

$$H_0: RR_{RAD} \leq RR_{PLB} \quad \text{versus} \quad H_1: RR_{RAD} > RR_{PLB},$$

where  $RR_{RAD}$  is the probability of angiomyolipoma response on RAD001 and  $RR_{PLB}$  is the probability of angiomyolipoma response on placebo.

Angiomyolipoma response rates will be provided with exact 95% confidence intervals ([Clopper and Pearson 1934](#)). The analysis will be performed using data up to the data cut-off date of the trial, which will be 6 months after the last patient is randomized.

### 10.4.3 Handling of missing values/censoring/discontinuations

Patients with unknown angiomyolipoma response status will be treated as non-responders in the calculation of the angiomyolipoma response rate in the FAS at the end of the trial.

Other missing data will simply be noted as missing on appropriate tables/listings.

#### 10.4.4 Supportive analyses

Potential effect of covariates (prognostic factors) will be investigated using exact logistic regression. The objective of this analysis will be to explore the sensitivity of the statistical significance of treatment effect on angiomyolipoma response rate after adjusting for main prognostic factors. Odds ratios will be used as a measure of association between treatment and response, presented with exact 95% confidence limits. These analyses are considered as supportive.

The first model will include treatment group and the protocol stratification factor as covariates (refer to [Section 10.4.2](#)). In a second model, the consistency of the treatment effect will be examined in the presence of possible prognostic factors, as described in Table 10-1, in addition to the stratification factor.

**Table 10-1 Definition of potential prognostic factors**

| Prognostic Factor         | Definition                                            | Model covariate definition  |
|---------------------------|-------------------------------------------------------|-----------------------------|
| Polycystic kidney disease | Presence of polycystic kidney disease at baseline     | POLYC (1=present, 0=absent) |
| Angiomyolipoma volume*    | Sum of volumes of target angiomyolipomata at baseline | VOLUME (continuous)         |

\* As determined by Independent Central Radiological Review using the baseline CT/MRI.

The best percentage change from baseline angiomyolipoma volume (defined as the sum of the volumes of the target angiomyolipomata) will be presented graphically by means of a waterfall plot, shown separately for each treatment group.

The primary analysis of angiomyolipoma response rate will be repeated in the Per Protocol Set.

#### 10.5 Secondary objectives

The secondary efficacy objectives were to compare RAD001 against placebo with respect to time to angiomyolipoma progression and skin lesion response rate. In order to be able to make a claim on either of these two endpoints, a multiplicity adjustment will be implemented (see [Section 10.5.3](#)).

##### 10.5.1 Time to angiomyolipoma progression

Time to angiomyolipoma progression (TTAP) is defined as the time from the date of randomization to the date of the first documented angiomyolipoma progression, as defined in [Section 7.5.2](#). TTAP will be censored if angiomyolipoma progression is not observed before (i) the cut-off date for the final analysis, or (ii) the date when a non-study systemic anti-angiomyolipoma therapy is started, or (iii) the date of death. The censoring date will be the date of the most recent CT/MRI assessment before the first of any of these three events occurred.

If angiomyolipoma progression is observed after two or more missing or non-evaluable CT/MRI assessments, then the date of angiomyolipoma progression will be censored at the latest occurring CT/MRI. For angiomyolipoma progression observed after a single missing or non-evaluable CT/MRI, the actual date of angiomyolipoma progression will be used.

TTAP will be compared between the RAD001 and placebo arms in the FAS using a one-sided logrank test at the 2.5% level stratified by the protocol stratification factor (TSC and use of EIAED versus TSC and non-use of EIAED versus sporadic LAM).

The TTAP distributions will be presented descriptively in the FAS using Kaplan-Meier curves. Summary statistics from the Kaplan-Meier distributions will be determined, including the median TTAP and the proportions of patients remaining progression-free at 6 and 12 months. These statistics will be given as point estimates with 95% confidence intervals.

The hazard ratio with a 95% confidence interval will be derived from the Cox proportional hazards model, stratified by the protocol stratification factor (TSC and use of EIAED versus TSC and non-use of EIAED versus sporadic LAM).

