Safety evaluations are routinely performed at each visit according to the visit schedule ([Table 7-1](#)). Patient must be in a fasting state (at least 12 hours) at the time of blood sampling for all laboratory evaluations including the lipid profile. Hematology and biochemistry evaluations will be performed according to the visit schedule ([Table 7-1](#)). Note that hematology and biochemistry assessments are performed at screening and do not need to be repeated on Treatment Day 1 if Treatment Day 1 occurs within 14 days of the screening visit. Otherwise, the patient will need to repeat the screening visit blood collections. All blood samples obtained at each visit will be sent to a Central Laboratory for analysis. If laboratory results are requested on an urgent basis, the attending physician will use the local laboratory results for treatment decisions. Complete details regarding all study required safety assessments are provided in [Section 7.6](#).

During this phase of the study, all patients will have a CT/MRI of the kidney performed at 12, 24 and 48 weeks after the start of study treatment, and annually thereafter until angiomyolipoma progression. A CT/MRI of the kidneys should be repeated at the End of Treatment (EOT) visit if the patient has discontinued for any reason other than angiomyolipoma progression, and if it has been more than 8 weeks since their most recent kidney CT/MRI during the first year of treatment, or more than 6 months since their most recent kidney CT/MRI thereafter.

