#### **4.5 Extension phase**

There are two distinct parts of this trial, the core and extension phase. The core phase is from the start of the trial up to the time when the results of the final primary analysis are known. This primary analysis will be performed using all data up to the data cutoff date, which is defined as 6 months after the last patient is randomized. Following a database freeze, the statistical analysis will be performed. During this time, patients will continue on the blinded treatment phase or open-label phase as before, until the time when the results of the final data analysis are known and the core phase of the trial is terminated.

If this final data analysis fails to show superiority of RAD001 over placebo, all patients will be discontinued from the study and will have end of treatment evaluations as indicated in [Table 7-1](#) and [Table 7-2](#). In this case there will be no extension phase.

If the final trial results favor RAD001, then an extension phase will be launched. All patients still receiving study treatment at this time, as well as those being followed for post-treatment evaluation, will be given the option of starting open-label RAD001. Similarly, patients receiving open-label RAD001 at the end of the core phase will be offered to continue into the extension period. The extension phase will run until 4 years after the last patient was randomized, ensuring patient follow-up of 4-5 years (assuming patient accrual over a period of approximately 12 months).

Those patients entering the extension phase, who had previously only been receiving placebo, will have scheduled assessments beginning at Treatment Day 1 according to [Table 7-2](#). Patients that had been on active RAD001 prior to beginning the extension phase will simply continue their sequence of assessments, according to [Table 7-1](#) and [Table 7-2](#). Accordingly, patients that had been on active RAD001 in the Open-label phase prior to beginning the extension phase will simply continue their sequence of assessments according to [Table 7-2](#). Patients in the extension phase will continue to have the same safety and efficacy assessments as in the core phase until angiomyolipoma progression, with the exception of biomarker assessments and pharmacokinetic assessments which will not be performed in the extension phase.

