#### **10.5.4 Additional secondary efficacy analyses**

##### **Duration of angiomyolipoma response**

Duration of angiomyolipoma response is defined as the time from the date of the first angiomyolipoma response until the date of the first angiomyolipoma progression, where angiomyolipoma response and angiomyolipoma progression are as defined in [Section 7.5.2](#). Duration of angiomyolipoma response applies only to patients who achieve an angiomyolipoma response. Duration of angiomyolipoma response will be censored if angiomyolipoma progression is not observed before the first to occur out of (i) the cut-off date for the final analysis, or (ii) the date when a non-study systemic anti-angiomyolipoma therapy is started, or (iii) the date of death. The censoring date will be the date of the most recent CT/MRI assessment before the first of any of these three events occurred.

Duration of angiomyolipoma response will be summarized for patients in the RAD001 treatment arm only. A Kaplan-Meier curve will be constructed, and the median response duration will be presented along with 95% confidence intervals. In addition, the Kaplan-Meier estimates with 95% confidence intervals at 3, 6 and 12 months will be summarized.

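### The 12-month Kaplan-Meier estimates for angiomyolipoma progression and response duration have almost no routine kidney scan behind them at the primary cut-off

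*Protocol*

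**What the plan says.** Section 10.5.1 defines TTAP and asks for Kaplan-Meier summaries in the Full Analysis Set, including "the median TTAP and the proportions of patients remaining progression-free at 6 and 12 months", with 95% confidence intervals. For patients without progression, observation ends at the cut-off, at a new systemic therapy or at death, and "The censoring date will be the date of the most recent CT/MRI assessment before the first of any of these three events occurred".

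Under the duration of angiomyolipoma response in section 10.5.4 (RAD001 arm only), the same censoring applies and "the Kaplan-Meier estimates with 95% confidence intervals at 3, 6 and 12 months will be summarized".

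Section 4.2 sets the imaging: "CT/MRI of the kidney performed at 12, 24 and 48 weeks after the start of study treatment, and annually thereafter". Table 7-1 allows 7 days either side. The cut-off is fixed in section 10.4.2, "which will be 6 months after the last patient is randomized", and section 4.5 plans follow-up "assuming patient accrual over a period of approximately 12 months".

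**The concern.** A Kaplan-Meier estimate at 12 months needs patients who are still under observation at 12 months. Under this censoring rule a patient counts as observed only up to the last scan, however long he or she has been in the trial. The last routine scan before the cut-off falls shortly before 12 months, and the next one falls after the cut-off.

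TTAP ranks first among the secondary endpoints in section 10.5.3, so its 12-month proportion is likely to be quoted. A reader would take it as an ordinary landmark estimate. In fact it would be missing, or it would be a curve tail driven by the order in which patients happened to be scanned within a two-week window.

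**Working it through.** The protocol states no figure for these estimates, so there is none to reproduce. The check is calendar arithmetic followed by simulation.

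**Calendar** (30.44 days per month)
- Follow-up at cut-off: 6 months to 12 + 6 = 18 months, i.e. 26 to 78 weeks.
- Last routine scan before cut-off: week 48 = day 336 = 11.0 months; latest day 336 + 7 = 343.
- Twelve months = day 365 = week 52.2.
- Next annual scan: week 96 to 100, beyond the 78-week maximum for everyone.
- Share of patients reaching week 48 by cut-off, with uniform accrual: (18 − 11.04)/12 = 58%.
- Accrual needed before anyone reaches the next annual scan: about 22.1 − 6 = 16 months (week 96) or 23 − 6 = 17 months (week 100).

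**Response duration on routine scans**
- First response at week 12: 48 − 12 = 36 weeks = 8.3 months.
- First response at week 24: 48 − 24 = 24 weeks = 5.5 months.
- First response at week 48, confirmed near week 60: 12 weeks = 2.8 months.

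None reaches 12 months.

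**Why the tail falls**

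About 58% of 33 placebo patients, some 19, would have a week-48 scan. Within the window, each patient with a clean scan leaves the risk set on the actual scan day. A progression found late in the window is then divided by the few patients not yet scanned. If it is found in the last patient scanned, the curve drops to zero.

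**Simulation**

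Assumptions: 33 placebo patients, uniform 12-month accrual, scans spread over ±7 days, exponential progression. The progression rates are assumed. The table gives the mean Kaplan-Meier value carried to 12 months.

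| Assumed true 12-month rate | Mean estimate | Shortfall |
|---|---|---|
| 90% | 83% | 7 points |
| 70% | 52% | 18 points |
| 50% | 30% | 20 points |

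- Without discontinuation, nobody was at risk at day 365.
- With an assumed 15% annual discontinuation followed by annual scans, at least one placebo patient was at risk in about half of the runs. The shortfall was then 6 to 16 points.
- A separately built simulation, without discontinuation, gave 80%, 52% and 29%: shortfalls of 10, 18 and 21 points. Over assumed true rates from 50% to 95%, its estimate was undefined in 78% to 99% of runs and fell to zero in 1% to 23%.
- Read at week 48 on nominal visit dates, the mean was 0.911 against a true 0.908, and 0.721 against 0.720.

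**Between arms**

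The shortfall grows with the progression rate. In a two-arm simulation with 5% of RAD001 patients having a week-60 scan, a true difference of 20 points (70% against 90%) appeared as 31, one of 10 (80% against 90%) as 17, and one of 5 (90% against 95%) as 9. With equal true rates the arms differed by only 0 to 2 points.

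**Longer accrual**

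At 18 months of accrual, 1 to 2 of 33 placebo patients are at risk at 12 months. At 24 months it is 7 to 9, and the shortfall is small (88% against 90%, 65% against 70%).

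**The case against.** The best reply is that some scans do pass 12 months, in either arm:
- Patients who stop treatment without progression have annual scans (sections 4.4 and 6.7.4). Someone stopping at weeks 12 to 24 is scanned at about weeks 64 to 76.
- Clinical suspicion of progression calls for prompt imaging (section 4.2).
- An end-of-treatment scan becomes due once more than 6 months have passed since week 48, from about week 74.
- A response first seen at week 48 is confirmed near week 60.
- Bleeding of grade 2 or worse counts as progression without a scan.

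This stands. A reader might infer that nobody can be at risk at 12 months, or that a 12-month response duration is impossible. The protocol does not support either: a week-12 responder who stops after confirmation at week 24 could be scanned near week 76, a duration of 64 weeks. But these routes yield a few selected patients, not a usable risk set.

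A reader might also infer that week-60 scans on RAD001 responders tilt the comparison. At equal progression rates that effect is negligible. Any inflation comes from placebo progressing faster.

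It is also fair that the summaries are descriptive, that accrual is an expectation and not a fixed design value, and that the protocol states no rule for carrying a curve past its last censored time. Handling of ties and of non-estimable values may be settled in an analysis plan. However, the protocol itself names the time points, and an analysis plan cannot supply the scans.

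**Conclusion.** The point holds. Under the protocol's own schedule, cut-off, censoring rule and expected accrual, the 12-month progression-free proportion lacks routine scan support and would usually be not estimable. Where a number is produced or carried forward, it is low by about 6 to 8 points at an assumed true 90% and 13 to 20 points at an assumed 50% to 70%; one build of the simulation reached 10 and 21. These sizes depend on the assumed progression rates and on the spread of scan days. The apparent difference between arms can be inflated when placebo progresses faster. The 12-month angiomyolipoma response-duration estimate lacks routine support beyond 36 weeks.

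The 6-month TTAP proportion is supported by the week-24 scan. The 12-month skin-response duration is a separate matter, because skin is assessed every 12 weeks. The log-rank test, the testing hierarchy and the primary analysis are not affected.

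**What to change.** - **Section 10.5.1:** give the descriptive progression-free proportions at week 24 and week 48 in place of 6 and 12 months. For this landmark summary only, assign scans inside the visit window to the nominal visit, with events counted before censorings at ties. Keep actual dates for the TTAP definition, the log-rank test and the Cox model. Show numbers at risk.
- **Section 10.5.4:** drop the 12-month angiomyolipoma response-duration estimate at the primary cut-off. Keep 3 and 6 months with numbers at risk, noting that on routine scans the 6-month value rests on week-12 responders.
- **12-month values:** report them only in a later extension-phase update that includes the next annual scan, and state there how placebo patients who have started open-label RAD001 are handled.

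No scan is added. The sponsor loses the 12-month label at the primary cut-off, and the landmark table uses a different date convention from the log-rank test, which a footnote should say.
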